## Abstract

**Background:**

Young adults from racial and ethnic minority (REM) groups are at greater risk of disengaging from vital mental health services than their majority group peers. Emerging research suggests developmentally tailored interventions that enable personalized exploration of cultural and structural contexts; encourage trust in relationships with service providers; enhance hope for recovery; and increase self-efficacy to adhere to treatment can improve engagement among underserved REM young adults with mental health disorders.

**Objective:**

Just Do You is a brief young adult treatment engagement intervention. Although Just Do You showed evidence of efficacy with medium effect sizes in a previous clinical trial, not all participants benefited, and some of the proposed mediators were not changed. Grounded in the multiphase optimization strategy (MOST), we propose to improve the provision and effects of Just Do You by testing a set of new candidate intervention components that complement the original Just Do You program. This can potentially enhance its effects on engagement and mental health service use for REM young adults.

**Methods:**

A total of 3 new candidate behavioral intervention components and their putative mediators were designed in collaboration with REM young adults and other key informants. The new candidate components and their mechanisms of action are (1) cultural identity (perceived cultural competency), (2) future self (hope), and (3) understanding environments (self-efficacy). A pilot optimization randomized controlled trial will be conducted in an outpatient mental health setting with REM participants aged 18-34 years (N=80). The candidate components will be tested in a 2^3^-factorial design where all participants will receive Just Do You and be randomly assigned to one of 8 experimental conditions, each composed of a unique combination of candidate components. We will assess the new components’ acceptability and feasibility, and explore preliminary evidence of their effects on the primary outcome (engagement in mental health care) and mediators at a 3-month follow-up assessment.

**Results:**

The study began recruitment in December 2024 and is planned to continue through December 2026. Final study completion is planned for March 2027. The results will be disseminated via professional and scientific publications, presentations, and social media, as well as to members of the participant community.

**Conclusions:**

Findings from this study will supply critical deployment-focused evidence to inform a future randomized controlled trial as the next step in this program of research. We ultimately aim to create an effective, efficient, and scalable intervention to improve engagement and mental health outcomes among REM young adults.

**Trial Registration:**

ClinicalTrials.gov NCT06508450; https://clinicaltrials.gov/study/NCT06508450

**International Registered Report Identifier (IRRID):**

DERR1-10.2196/68885

## Introduction

### Background

In the United States, young adults (aged 18-34 years) with mental health disorders who are from racial and ethnic minority (REM) groups are at high risk for withdrawing from mental health treatment prematurely [1], particularly those with lower socioeconomic statuses [2]. Younger adults in general have lower rates of treatment for their mental health concerns than any other age group [3]. Among young adults with serious mental illness (SMI; eg, schizophrenia-spectrum and mood disorders), poor adherence to mental health care is associated with significant health and social disadvantages (eg, poverty, incarceration, and early mortality) [4,5]. On the whole, staying engaged in mental health treatment leads to improvements in health outcomes and mental health recovery [6]. However, there is very little evidence-based interventions designed for increasing the participation of young adults with mental health disorders in treatment [7], and studies show disparities in outcomes for REM groups [8,9].

### Engagement Interventions Tailored for the Transition to Adulthood

Adult mental health services are not generally equipped to address the developmental complexities of young adulthood, and typically lack services and interventions adapted specifically for young adults [10,11]. Young adulthood is an exploratory period marked by transitions and instability in various areas of life (eg, residential status, work, school, and social relationships) [12]. Treatment adherence can be a challenge under these circumstances, especially considering that young adults gain greater responsibility and autonomy over their mental health care during this developmental period [13,14]. Stopping and starting treatment is common. Because symptom onset often occurs around this age [15], deciding to drop out of treatment is risky for young adults with SMI. Without treatment, SMI symptoms can place significant constraints on developmentally appropriate exploration [16] and successful life transitions [4,17]. Recent approaches to maintaining engagement in mental health care during the transition to adulthood target individuals ranging from 15 to 35 years old [18], and have primarily focused on expanding adolescent and family service models [19-21]. However, research suggests that young people with mental disorders become less engaged with treatment once they enter adult systems of care [4,22], and that marginalized young adults may not have access to family members who can provide support [16,23].

Developmentally tailored approaches that focus on improving mental health care literacy and self-efficacy have the potential to improve engagement in treatment among REM young adults with mental health disorders [21]. Studies show REM young adults report apprehension and uncertainty about the nature of treatment and the processes for accessing it [24,25]. Research on mental health help-seeking among young adults indicates that negative perceptions about treatment play a significant role in their reluctance to initiate care [14,26]. Young adults with mental health conditions report that treatment services can seem irrelevant and unhelpful [27], and they experience stigma [28,29] and hopelessness about the future [30] that can present barriers to engagement in services [31].

### Person-Centered, Culturally Responsive Interventions

Interventions that target cultural and intersectional factors along with developmental stage are essential for engaging REM young adults living with mental health disorders [20,21,32]. The most intensive exploration of racial, ethnic, and other key social identities often happens during young adulthood [33], and informs an individual’s sense of self and direction in life [34]. REM young adults have expressed hesitancy about mental health treatment due to historical and current racism in health care [35], differences in perceived need for mental health care [36], and cultural beliefs and preferences around how to address mental health problems [37]. Studies show that REM young adults experience structural vulnerabilities (eg, living in high poverty areas, more coercive rather than voluntary treatments) [38], report low cultural competency among mental health care providers [39], along with high levels of mistrust of providers [24], which serve as key barriers to participating in treatment. Research on REM young adults in mental health care indicates that they desire greater knowledge and understanding of their identities and social positions by mental health professionals [25].

Culturally responsive interventions can improve treatment engagement by facilitating communication about the cultural and structural context from the young adult’s perspective [40]. This allows treatment providers to be responsive to young adults’ experiences and identify barriers that can arise and strengths that can be drawn upon in treatment [41-43]. Mental health interventions adapted for REM youth have incorporated culturally relevant elements (eg, language, metaphors, values, and traditions) for specific racial-ethnic groups [44]. But, adapting intervention protocols for each cultural group is not feasible for public and community mental health services that will likely provide care for youth from a wide range of backgrounds [42,45]. Also, interventions adapted for a specific racial-ethnic group may not be able to address an individual young person’s intersectional social positions (eg, gender, sexuality, wealth, immigration, and multiracial-ethnic statuses) that influence their mental health and experiences of mental health care [42]. Recent research on cultural adaptation favors person-centered approaches that invite discussion of cultural and structural factors, and allow individuals to articulate what matters most about their identities, without the need to adapt intervention protocols for prespecified aspects of cultural identity [46,47].

### Just Do You Intervention

This study tests 3 new candidate behavioral intervention components focused on cultural and structural content that can potentially be added to the Just Do You intervention in order to improve its effects for REM young adults with SMI. Just Do You [48] is an evidence-informed treatment engagement intervention that uses narrative health communication, role models, and expressive arts in a brief curriculum aimed at orienting young adults to treatment in adult mental health care settings. As young people become familiar with the staff at a clinic and the services that are available, they form impressions about treatment that allow them to make informed decisions about whether to continue. The overall goal of Just Do You is to provide an orientation to mental health treatment that will support both initial and ongoing service engagement [49]. Just Do You is delivered by a clinician and a professional peer who is further along in their mental health recovery and life experiences (a Recovery Role Model) who facilitates conversations and expressive activities based on the orientation content. This cofacilitator approach models for young adults how to collaborate with professionals in their treatment. The developmentally tailored curriculum conveys information about mental health treatment and clinic services to young adults through credible sources (eg, peer and celebrity testimonials) and multisensory activities (eg, art therapy directives) designed to hold their attention and positively shape their perceptions about treatment, stigma, and service providers [49]. In a recent randomized controlled trial (RCT) conducted at 4 sites associated with 2 large urban mental health organizations in the eastern United States (ClinicalTrials.gov, NCT03423212), Just Do You demonstrated feasibility, acceptability, and efficacy for improving treatment engagement and personal mental health recovery at 3 months after baseline, with a medium effect size, among a sample of 121 young adults with SMI, 95% of whom were from Black, Latinx, and multiracial minoritized groups [50,51].

Just Do You is based on the young adult framework of mental health service use [24]. The young adult framework was developed through studying young adults with mental health disorders and applying theories of behavior change [52,53] and mental health service use [54] to describe the phenomenon of disengagement from treatment during the transition to adulthood. Just Do You was designed to target mechanisms of engagement in services identified by the young adult framework through developmentally tailored behavior change techniques [55]. In the most recent clinical trial described above, Just Do You demonstrated statistically significant effects on four proximal mediators from the young adult framework: (1) perceived advantages of treatment, (2) trustworthiness and (3) credibility of treatment providers, and (4) stigma surrounding service use. The young adult framework was validated by trial results, but Just Do You did not impact all targeted mediators [50], including hope and self-efficacy, suggesting the need for further culturally tailored adaptations to strengthen the intervention’s influence on theoretical mechanisms of engagement and service use, as well as mental health outcomes.

### Conceptual Model

Results from the original Just Do You trial, along with findings from previous research discussed above, suggest that adding select behavioral intervention components may boost the effects of Just Do You on key mediators for REM young adults. Participant data in the original Just Do You trial across both treatment and control conditions showed that REM young adults had strong racial-ethnic identities (ie, sense of belonging and connectedness to their racial-ethnic groups) [35,56], and that strong racial-ethnic identity was associated with treatment engagement through increased hope, self-efficacy, and provider credibility ratings [57]. Building upon the conceptual model for the previous trial of Just Do You, we have designed 3 new candidate behavioral intervention components to address important mediators for REM young adults (Figure 1). The new candidate components expand upon these findings regarding the importance of racial-ethnic identities and the salience of structural barriers, and they add content to improve cultural and structural competency practices in mental health [46,58]. The new candidate behavioral intervention components seek to (1) enhance perceived cultural competency of providers, (2) improve hope (ie, self-belief and outcome expectancy that recovery is possible), and (3) improve self-efficacy for treatment engagement (ie, decrease perceived difficulty or increase control of engagement behaviors). Hope and self-efficacy were targeted as mediators in the previous trial of Just Do You but did not change [50].

**Figure 1 figure1:**
[figure not shown]
Conceptual model.

### Candidate Behavioral Intervention Components

#### Overview

The new candidate components are designed to explicitly address person-centered cultural and structural content while targeting the proposed mediators of engagement specified in the conceptual model. The candidate components were selected by the first author in consultation with the research team, which included a creative arts therapist and the creator of Just Do You. All candidate components maintain the theoretical framework and delivery approach of the original intervention. The components use narratives, role models, and creative arts to preserve fidelity to the original Just Do You curriculum’s evidence-informed health communication strategies. Each candidate component was selected to meet these criteria based on preliminary research, and they were collaboratively designed using the ADAPT-ITT (Assessment, Decision, Adaptation, Production, Topical experts-integration, Training, and Testing) model [59]. ADAPT-ITT is a well-established participatory approach for modifying interventions to be effective with a specific target population. Through this process, new components were designed with REM young adults and mental health professionals, including peer service providers, in community-based adult psychiatric services. Our year-long collaborative design project produced versions of the candidate components that are more likely to be acceptable, feasible, and effective in adult community mental health settings. The 3 new candidate components, and their respective training and fidelity protocols, were manualized and formatted to complement the Just Do You core intervention as additional sessions.

#### Component A

Cultural identity is based on recent advances in cultural identity-affirming psychosocial interventions for youth [60,61] and the Cultural Formulation Interview (CFI) for *DSM-5* (*Diagnostic and Statistical Manual of Mental Disorders* [Fifth Edition]) [46]. Research suggests rapport-building strategies that prompt positive cognitions about culture in REM young adults can communicate, both implicitly and explicitly, that their cultural identities are important and will be respected within the therapeutic relationship [62]. The CFI guides mental health service providers to initiate conversations about the cultural context of individual patients at the start of treatment, in order to better address barriers that can arise and identify cultural strengths that can be drawn upon in clinical care. The CFI has been shown to enhance initial health communication and therapeutic rapport [63], and improve ongoing treatment attendance among adults and youth from minoritized racial-ethnic groups in outpatient mental health treatment [42,43].

#### Component B

Future self draws upon concepts from solution-focused brief therapy [64] and identity-based motivation in health [65] to help young adults generate positive, culturally relevant imagery of their future selves and connect those images to sustained engagement in mental health services. Solution-focused brief therapy techniques explicitly focus on generating hope and receptivity to new thoughts and actions [66]. Identity-based motivation techniques involve framing the actions needed to attain a desired future as congruent with social identities that are most salient to a young person [67]. Component B also uses elements of Photovoice [68], in which young adults take photos or videos to express a narrative storyline about their future self in recovery. Photovoice has been used as a mental health recovery intervention for people living with SMI [69,70], and previous studies highlight the utility of this approach and its alignment with the narrative and creative arts strategies in Just Do You [69,71].

#### Component C

Understanding environments draws from the structural competency framework [72] to address social and environmental factors that shape REM young adults’ engagement in mental health services (eg, unstable housing, poverty, community violence, and community protective factors). Using elements from neighborhood mapping [73,74], the professional peer facilitator (Recovery Role Model) initiates planning with young adults to manage barriers and increase their self-efficacy to sustain engagement. This approach makes use of the peer support strategy already employed in Just Do You, and previous research indicates that working with peers who relate to their social challenges is associated with greater outpatient engagement [75] and reduced disparities in service use among REM young adults with mental health disorders [76].

### Multiphase Optimization Strategy

This study will examine the new candidate intervention components using the multiphase optimization strategy (MOST) [77]. MOST is a principled method for identifying the optimal combination of intervention components before testing an intervention in a resource-intensive RCT [78]. The MOST framework consists of 3 stages: preparation, optimization, and evaluation of the intervention in a standard 2-arm RCT. This pilot trial comprises the preparation stage of MOST, in which we will pilot the study protocols to enroll and assess participants and deliver the components in a community mental health setting using a factorial design. The pilot optimization trial will establish the feasibility and acceptability of the approach and the candidate components in the intervention setting, and explore preliminary evidence of components’ effects on study outcomes and mediating variables, in preparation for a future fully powered optimization RCT.

### Study Objectives

The overall goals of our pilot research are (1) evaluate the acceptability and feasibility of the new candidate intervention components, (2) explore preliminary indications of components’ impact on engagement and service use (ie, active involvement and attendance to treatment) and on hypothesized mediators at 3-month follow-up, and (3) refine aspects of the approach for a future optimization RCT (eg, implementation, recruitment, and assessment strategies). We will test the new candidate components with REM young adult participants in an outpatient community mental health setting, using mixed methods to collect and integrate data from quantitative measures and qualitative interviews.

## Methods

### Pilot Trial Design

This study uses a balanced 2^3^ factorial experiment. Each factor will have 2 factor levels, included (yes) or excluded (no), resulting in 8 experimental conditions that represent all possible combinations of the new candidate components (see Table 1). All participants will receive the Just Do You core component, followed by the candidate components they were assigned to receive, if any. Thus, participants will be randomly assigned to one of 8 experimental conditions and receive Just Do You and 0-3 new components. We will explore preliminary evidence of component effects on the primary outcomes by comparing the mean outcomes across included conditions versus the mean outcomes across excluded conditions. For example, Component A conditions 5-8 will be compared to conditions 1-4. The factorial design does not directly compare each condition or use a traditional control group. Instead, each factor level serves as its own control. Consistent with a convergent parallel mixed methods design [79], semistructured qualitative interviews will be conducted postintervention with participants to provide context and improve our interpretation of quantitative results. A total of 80 participants will be enrolled.

**Table 1 table1:** Experimental conditions in the 23-factorial design.

Experimental condition	Just Do You	Component A	Component B	Component C	Sample size, n
1	Yes^a^	No^b^	No	No	10
2	Yes	No	No	Yes	10
3	Yes	No	Yes	No	10
4	Yes	No	Yes	Yes	10
5	Yes	Yes	No	No	10
6	Yes	Yes	No	Yes	10
7	Yes	Yes	Yes	No	10
8	Yes	Yes	Yes	Yes	10

^a^Yes: component is included.

^b^No: component is excluded.

### Study Setting

Young adult participants will be recruited from an outpatient psychiatric rehabilitation program (the study site) in the eastern United States that serves a community of primarily adult Black and Hispanic or Latine individuals. Mental health services offered by the study site include therapeutic and skills-based group treatment, individual counseling, medication support, and resource coordination for transportation, housing, employment, and other recovery supports.

### Eligibility Criteria

Young adult participants will be eligible if they are between the ages of 18 and 34 years, identify as REM (ie, from racial and ethnic groups other than non-Hispanic, White), and are enrolled in mental health services at the study site. The eligible age range is consistent with definitions of young adulthood by the United States Census Bureau [80] and the age range most commonly targeted in early intervention services for SMI [18]. Participants will be excluded if they cannot comprehend and speak English or if they cannot understand the consent process.

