### Recruitment

Participants will be recruited through flyers distributed by the research team that briefly describe the study and how to contact research staff for more information. Research staff will be present at the study site on a weekly basis to provide information in person. Interested participants who make contact with the research staff will be offered a brief eligibility screening. Participants who are eligible will be asked to provide their informed consent for enrollment.

Recruitment activities are planned to take place over 24 months. Administrative staff at the study site reported that there are about 30 young adults meeting eligibility criteria enrolled in the clinic services at any given time, with about 4 new enrollments per month. We estimate a 10% refusal rate based on the low rates of refusal in the previous Just Do You trial, which will allow us to recruit the sample over 24 months. To enhance tracking and retention for follow-up assessments, we will collect extensive contact information for all participants, which includes contact information for up to 3 individuals who will be able to locate them, and use reminder calls or texts for assessment appointments.

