Engagement in treatment will be measured using 8 items from the Client Engagement in Child Protective Services Scale involvement or buy-in subscale [83]. Responses are on a 5-point Likert scale. An example item is “I am not just going through the motions. I’m really involved in working with providers.” The range for the scale is 8 to 40, with higher scores indicating higher levels of engagement. This scale has demonstrated acceptable reliability with the study target population (=.82) [51,83]. Service usage will be measured at a 3-month follow-up by participant medical records. The total number of contacts each participant makes with the treatment program, and the dates for all contacts, starting 1 month before baseline through 3-month follow-up, will be collected to assess change in service use over the study period. Demographic information will be collected at baseline, and targeted mediators and mental health symptoms will be collected by self-report measures at all timepoints. Study measures have been extensively tested by the research team [84] and previous studies with REM populations, young adults, and individuals living with SMI. All have been found to have good psychometric properties. Can be found in Multimedia Appendix 2: Baseline assessment measures for a full list of the study measures collected during the baseline assessment.

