To assess treatment engagement outcomes, exploratory analyses will examine the distributions of all variables, identify outliers, and calculate descriptive statistics for each assessment timepoint, and with respect to the 3 components. We will use an intent-to-treat approach for the analysis. Factorial ANOVA using effect coding will be used to estimate the main effects and interactions between factors (ie, components) on the mean change in number of contacts with treatment services and the level of engagement at 3-month follow-up. Each intervention component will be assigned a value of +1 or –1 depending on whether it was included or excluded from the experimental condition (ie, yes or no). In addition, we will explore evidence of effects on mediators at posttest and 3-month outcomes. Analyses will rely on an examination of the overall pattern of changes (eg, strength and change in the intended direction) instead of hypothesis testing. The sample size of 80 is sufficient for the planned analyses and provides 79% power to detect main effects, corresponding to a correlation of 0.6 and a medium effect size (*d*=0.50), given α=.05.

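### For clients who join within a month of admission, the pre-baseline contact count includes days before they were clients, so mean change in contacts partly reflects entry to the clinic

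*Protocol article*

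**What the plan says.** Eligibility Criteria asks that participants fall in the age range, identify as REM "and are enrolled in mental health services at the study site". No minimum or maximum time since admission is set.

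Recruitment describes the source population: "there are about 30 young adults meeting eligibility criteria enrolled in the clinic services at any given time", "with about 4 new enrollments per month". On timing and uptake it says "Recruitment activities are planned to take place over 24 months" and "We estimate a 10% refusal rate". It does not say how soon after admission a new client would be approached.

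Measures fixes one window for everyone. Contacts and their dates, "starting 1 month before baseline through 3-month follow-up, will be collected to assess change in service use over the study period".

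Data Analysis names the outcomes of the factorial ANOVA as the "mean change in number of contacts with treatment services and the level of engagement at 3-month follow-up". It adds that interpretation will rest on the size and favourable direction of change, not on hypothesis tests. Randomization describes blocks over the eight conditions and states no balancing on time since admission.

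**The concern.** The one-month look-back assumes that every participant could have attended during that month. A client admitted less than a month before baseline could not have attended as a client on the days before admission. Those days count as zero, so the pre-baseline count is low by construction. For an established client, the same month is a true usage level.

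Averaged together, the two kinds of change score give a figure that mixes entry to the clinic with change in attendance. The artefact has the sign that the plan would read as benefit. A pilot that looks at patterns of change has no test or comparator to discount it when the overall or within-level mean change is described. These figures are meant to inform the larger optimization trial.

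**Working it through.** **Recruitment mix** (inputs from Recruitment; N = 80 from Pilot Trial Design)
- Pool: 30 + 4 × 24 = 126. After 10% refusal: 0.9 × 126 = 113.4. This exceeds 80, so the article's statement that the sample can be recruited in 24 months follows from its own figures.
- Existing clients who could join, at most: 0.9 × 30 = 27.
- Participants admitted after recruitment opens, at least: 80 − 27 = 53, and 53/80 = 66%. With recruitment proportional to the pool: 96/126 = 76%, about 61 of 80.

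These are not the shares affected. Only clients who join within a month of admission have a shortened pre-baseline month, and that share is not given. If recruitment were spread evenly over clients' time at the clinic (assumption), it would be about 4/30 = 13%. Earlier approach to new clients would raise it. I therefore use 13% to 76% as a range.

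**One client's change** (assumed 4 contacts a month before and after, follow-up expressed per month, no contacts before admission)
- Established: 4 − 4 = 0.
- Admitted one week before baseline: pre-baseline count 4 × 0.25 = 1, change 4 − 1 = +3.
- Admission dates spread evenly over the month: average pre-baseline count 4 × 0.5 = 2, average change +2. At 8 contacts a month it is +4.

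**Overall mean change with no true change** = share affected × average shift
- 13% at 4 a month: 0.13 × 2 = +0.26
- 25% at 4 a month: 0.25 × 2 = +0.5
- 76% at 8 a month: 0.76 × 4 = +3.0

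**Chance imbalance in a 40-versus-40 contrast**, one-week case (shift 3), SD = 3 × √(p(1−p) × 2/40)
- p = 13%: 0.23
- p = 25%: 0.29
- p = 50%: 0.34
- p = 66%: 0.32 contacts a month

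With dates spread evenly at 4 a month, the shift has mean 2 and mean square 16/3. The SD is then √{[p × 16/3 − (2p)²] × 2/40}: 0.18 at 13% and 0.30 at 66%.

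**Net effect on precision.** A shortened month also carries less count noise, so the imbalance term is not all added error. One-week case at 66%, Poisson counts, 4 a month:
- No between-person variation. Established variance: 4 + 4/3 = 5.33. Recent: 1 + 4/3 = 2.33. With the mix: 0.66 × 2.33 + 0.34 × 5.33 + 9 × 0.66 × 0.34 = about 5.4, against 5.33 without it. The contrast SE is 0.52 either way.
- Between-person coefficient of variation (CV) 0.5. Recent variance rises by 0.75² × 4 = 2.25 to 4.58. With the mix: 0.66 × 4.58 + 0.34 × 5.33 + 2.02 = 6.85. SE = √(6.85 × 2/40) = 0.585, against 0.516.

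Simulated gamma-Poisson contacts (mean 4 or 8 a month, CV 0.4 or 0.6, dates spread evenly, 25% to 76% recent) gave a change-score SD between 2.47/2.31 = 1.07 and 4.51/3.27 = 1.38 times its value with no recent admissions. The pre-post correlation fell from 0.51–0.82 with none to 0.34–0.58 at 76%.

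**Link to the stated power.** Data Analysis gives 79% for d = 0.50 with correlation 0.6.
- Baseline adjustment: SD √(1 − 0.36) = 0.80, and 0.5 × √20/0.80 − 1.96 = 0.835, power 79.8%. This reproduces the figure.
- Change score: SD √(2 × 0.4) = 0.894, and 0.5 × √20/0.894 − 1.96 = 0.54, power 70.5%.

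So the stated power matches an adjusted analysis rather than a two-sided analysis of raw change.

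**The case against.** A reader might infer more than the documents support.

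- *The component effects are biased.* They are not, in expectation. Components are randomised, so the entry effect is expected to be equal at both levels of each factor. Chance imbalance is ordinary sampling error already carried in the interval. If blocks hold eight and existing clients mostly join early, blocking in enrolment order also balances some of it.
- *Two thirds of the sample are affected.* The 66% counts people admitted after recruitment opens. Recruitment is by flyers and weekly staff presence, not stated to occur at intake, so the share joining in their first month is unknown.
- *Change in contacts measures entry instead of engagement.* For a client with no prior time at the clinic, change equals follow-up attendance, which is service use. The measure is a mixture. Including new clients fits an intervention meant to orient people to treatment.
- *Self-reported engagement is distorted too.* The scale does not use the pre-baseline month, and its 3-month level is unaffected. Nothing in the text shows that new clients' baseline ratings are unreliable.

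It can also be said that covariates and subgroup displays belong in an analysis plan that is not shown, and that this is an exploratory pilot. That is fair for the detail. But the article itself fixes the look-back window and names mean change in contacts as the analysed outcome, and a descriptive reading of change is where the artefact misleads most.

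**Conclusion.** The point holds in a limited form. Open eligibility, a fixed one-month look-back and an analysis of raw change together make the overall and within-level mean change in contacts uninterpretable as a change in engagement. The randomised contrasts lose some precision and are open to chance imbalance, but are not biased in expectation.

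The size depends on figures the article does not give. The spurious mean change runs from about +0.26 contacts a month (13% affected, 4 contacts a month) to +3.0 (76%, 8 a month). The loss of precision in the contrast ranges from negligible to an SD 38% larger. Attendance rates, between-person spread and the share recruited in their first month are all assumptions. This is a worthwhile, inexpensive improvement to one outcome and not a flaw in the design as a whole.

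**What to change.** 1. Take each participant's admission date from the clinic record that is already to be extracted.
2. In Data Analysis, replace raw change in contacts with post-baseline contacts to 3 months, adjusted for the pre-baseline count and an indicator for admission less than one month before baseline, with their interaction if wanted.
3. Report descriptive change in contacts separately for recently admitted and established clients.

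In simulation (assumed 4 contacts a month, CV 0.4 to 0.8, 13% to 66% recently admitted) this cut the contrast SE by about 7% to 29% against raw change. Most of that gain comes from adjusting for the pre-baseline count. The indicator mainly secures interpretation.

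The cost is one data field and one to three degrees of freedom. It works for participants already randomised, and randomisation need not change, so stratifying partway through is unnecessary. A pre-baseline rate per enrolled day is best avoided: one week after admission, 0, 1 or 2 contacts would imply 0, 4 or 8 a month, and the rate is undefined on the day of admission.
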